### **Neonatal participants in control group:**

Temperature: Temperature will be recorded at baseline and once daily before the swabs thereafter until discharge or 72 hours.

#### **4.7.2. Microbiology procedures for assessing efficacy**

Efficacy will be measured as change in colony forming units (CFUs) from baseline (the swabs at randomisation before antiseptic application).

To allow comparison across groups, all women in labour (regardless of randomisation group) will have a swabs taken at baseline (0 hrs), 4 hours, 8 hours, 24 hours, 28 hours, and 32 hours and all neonates (regardless of randomisation group) will have swabs taken at baseline, 24 hours, 48 hours and discharge or 72 hours.

Additionally, to provide an estimate of the effect of maternal intervention in the newborn, babies born to mothers in the maternal stratum will have swabs (peri-rectal/rectal and cervical/neck) taken after birth. The timing of these swabs will be recorded on a CRF.

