##### **4.5.5.2. Randomisation codes and unblinding**

The allocation will not be blinded as this is not practical given the number of factors evaluated. However, the primary end point (total bacterial load in colony forming units (CFUs)) is quantitative in nature and will be assessed by laboratory staff blinded to randomisation. See [Section 10.1.1](#) for further information.

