**4.6.2. Trial treatments**

At the point of recruitment baseline clinical and demographic data will be collected for all participants, and a baseline skin assessment performed and documented.

Participants in both strata, other than those randomised to the control group, will be randomised to either 1% CHG, 2% CHG or Octenidine dihydrochloride 0.1% phenoxyethanol 2% (OHP, trade name Octenisept®), at different frequencies ([see above](#)). Each application will be recorded in the appropriate CRF.

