An enrolment form will be completed and data entered into the database. Participants will be randomised ([Section 4.5.5.1](#)) and have baseline data collected, including medical history, gestational age, co-morbidities and antibiotic history.

Assessment and treatment regime will be according to allocation:

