### **4.10. Statistical considerations**

#### **4.10.1. Method of randomisation**

Randomisation codes will be generated using a random number generator, as implemented in common statistical software packages. The randomisation codes will be kept on an electronic database which the mobile device used by the clinical staff will connect to when they initiate the randomisation of a participant. The mobile device will, during this connection, retrieve the randomised treatment group allocation for the next participant on the randomisation list. The design will not be blinded as this is not practical given the factors evaluated. However, the efficacy endpoint (bacterial colonisation) will be assessed by laboratory staff blinded to randomisation.

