#### Primary analysis

- The primary analysis population is intention-to-treat, including all randomised participants, regardless of treatment received.
- The outcome variable will be change in Total log10 CFU from baseline to assessment time point.
- The primary analysis will include all randomised participants with baseline and at least one post-baseline measure.
- The dependent variable will be total log CFU.
- The model will be a mixed effects model
- Fixed effects in the model will be:
  - Antiseptic (1% CHG, 2% CHG, OCT)
  - Frequency of application (once, multiple)
  - Time point of assessment: hour of swab (continuous; mfp will be used to assess linearity)
  - Baseline total CFU (continuous; mfp will be used to assess linearity)
- Individual will be fitted as a random effect to account for repeated measures within individuals. Goodness of fit of an unstructured covariance matrix will be assessed and used if it is clearly a better fit to the data than random intercepts only.
- Goodness of fit of an interaction between baseline total CFU and timepoint of assessment will be assessed and included in the model if clearly a better fit.
- Normally distributed errors will be fitted.
- The intercept (reference treatment category) will be once only 1% CHG as this is the lowest concentration of CHG, which is believed to be more readily available than OCT, and so would be the most straightforward to implement. The standard of care control will not be used as the reference as the sample size for this arm is lower than for the factorial arms and so power for comparisons is correspondingly lower.
- Comparison of effects between factorial arms will be assessed by testing whether the null hypothesis of no treatment effect can be rejected (equivalent to using the estimate and 95% confidence interval of the estimate of the difference to the intercept).
- Comparisons between other arms and between arms and the SOC arm may also be performed. There will be no formal correction for multiple testing but interpretation will take multiple testing into consideration.
- Model fitting will use restricted maximum likelihood (REML) and p-values are derived using the Kenward-Roger approximation.

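### Baseline swabs and the first maternal toxicity score are scheduled after randomisation in an open-label trial, so baseline could differ, or be missing, by arm

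*Protocol*

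**What the plan says.** Protocol 4.7.2 measures efficacy as change in CFU from baseline, with baseline being "the swabs at randomisation before antiseptic application". Section 4.10.4 also adjusts the mixed model for the baseline value and takes all randomised participants as the primary population.

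In Table 1 (mothers) the columns run screening, randomisation, then the 0 h visit, which holds the first toxicity assessment and the first swabs. In Table 2 (neonates) the first swabs fall in the day-0 intervention visit, after the randomisation column. The text of 4.7.1.1 follows the same order: women are randomised and "have baseline data collected, including medical history, gestational age, co-morbidities and antibiotic history", and then "Assessment and treatment regime will be according to allocation". Section 4.7.1.2 is parallel for neonates.

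On blinding, 4.5.5.2 states: "The allocation will not be blinded as this is not practical given the number of factors evaluated". Section 4.10.1 repeats this and says that clinical staff retrieve the allocation on a mobile device. The stated protection is that the primary endpoint "will be assessed by laboratory staff blinded to randomisation".

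On the timing of baseline data, 4.6.2 says: "At the point of recruitment baseline clinical and demographic data will be collected for all participants, and a baseline skin assessment performed and documented".

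**The concern.** Taking the baseline before antiseptic is applied keeps a treatment effect out of it. It does not stop the person taking it from knowing the arm. Section 4.7.7 makes the research midwives responsible both for recruiting and for completing trial procedures, so the person swabbing or scoring at 0 h can know the allocation.

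Laboratory blinding protects the count on the plate. It does not protect how thoroughly the swab is taken, or the decision in 4.7.1.1 whether a soiled area is cleaned first. It also does not protect the toxicity score, which rests on reported irritation and visual inspection. Section 4.7.3 wants toxicity assessed at common time points so that arms can be compared without bias; a first score taken after allocation weakens that aim.

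The baseline matters twice over: it is the origin of the co-primary outcome and a covariate in its model. And because it is collected only after randomisation, a randomised participant can lack it altogether.

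**Working it through.** **1. Order of events, from the protocol.**

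| Measure | Where scheduled | Earlier value? |
|---|---|---|
| Maternal swabs | Table 1 and 4.7.1.1: 0 h, after randomisation | None |
| First maternal toxicity score | Table 1 and 4.7.1.1: immediately before the 0 h swabs | No formal score; 4.5.1.2 has only a clinician's eligibility judgement, and 4.6.2 a skin assessment at recruitment |
| Neonatal swabs | Table 2 and 4.7.1.2: day-0 visit, after randomisation | None |
| Neonatal temperature | Table 2: day-0 visit; 4.7.1.2: before application (baseline in controls) | None, but paired with the application by design |
| Neonatal skin score | 4.7.1.2: at screening; Table 2: only from the day-0 visit | The two places conflict |
| Baseline data, mothers | 4.6.2: at recruitment; Table 1 and 4.7.1.1: with or after randomisation | Not aligned |
| Baseline data, neonates | 4.6.2: at recruitment; Table 2: screening; 4.7.1.2: after randomisation | The places conflict |

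The order applies to all 2 × 147 = 294 randomised participants.

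**2. What an arm-related shift would do.** Let d0 be a shift in one arm's baseline, d1 a shift in its later swabs, and b the slope of the outcome on baseline. The bias is:

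- change score: d1 − d0
- baseline-adjusted: d1 − b·d0
- either analysis with a pre-allocation baseline (d0 = 0): d1

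The documents give none of these quantities. Assume a shift of 0.2 log10 CFU and b from 0.3 to 0.7.

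| Case | Adjusted, as scheduled | Change score, as scheduled | With pre-allocation baseline |
|---|---|---|---|
| Baseline only (d0 = 0.2, d1 = 0) | −0.06 to −0.14 (0.3 × 0.2; 0.7 × 0.2) | −0.20 | 0 |
| Same shift at every visit (d0 = d1 = 0.2) | 0.14 to 0.06 (0.7 × 0.2; 0.3 × 0.2) | 0 | 0.20 |

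**3. What missing baselines would do.** First, the plan's own power figures (4.5), from power = Φ(Δ·√[n1·n2/(n1+n2)] − z(1−α/2)) with SD = 1. For antiseptic against antiseptic: 0.82 × √21 − 2.512 = 1.246, so the power is 0.894.

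Now assume that a fraction of randomised participants, equal across arms, has no baseline and is neither analysed nor replaced:

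| Comparison | n | Effect (SD) | α | None missing | 5% | 10% | 20% |
|---|---|---|---|---|---|---|---|
| Antiseptic vs antiseptic | 42 vs 42 | 0.82 | 0.012 | 0.894 | 0.875 | 0.854 | 0.802 |
| Frequency vs frequency | 63 vs 63 | 0.58 | 0.05 | 0.902 | 0.887 | 0.870 | 0.829 |
| Antiseptic vs control | 42 vs 21 | 1.01 | 0.012 | 0.897 | 0.879 | 0.858 | 0.807 |
| Frequency vs control | 63 vs 21 | 0.90 | 0.025 | 0.908 | 0.892 | 0.874 | 0.830 |

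The stated 90% power is reproduced and is not in dispute. Keeping 147 participants with a baseline would need 147/0.95 = 155, 147/0.90 = 164 or 147/0.80 = 184 randomised per stratum. One missing baseline is 1/21 = 4.8% of an arm.

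**The case against.** The strongest objection is that later swabs are also unblinded. If swabbing effort differs by arm in the same way at every visit, a post-allocation baseline partly cancels the difference, and a pre-allocation one does not (second case in step 2). That is correct: the change protects the baseline, not the trial as a whole. But relying on two biases to cancel requires them to be equal and constant, which nothing in the protocol ensures.

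Second, nothing shows that a shift occurs. Counts are read blind, swab technique is set out in the manual of operations, and single- and multiple-application arms have the same steps at 0 h. This stands as a limit on size. It is weakest for control against antiseptic and for the toxicity score.

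Third, losses before 0 h should be few. Both steps fall on day 0, women in active labour are excluded (4.5.1.2), and 4.7.1.1 allows extra recruitment when swabs are missing. This too stands as to size, although extra recruits restore numbers and not the original randomised comparison. Swabs are tied to planned vaginal examinations (4.6.2.2, 6.2.1), so the gap need not be zero.

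A reader might infer more than the documents support:

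- **That the protocol drops these participants from the primary analysis.** It does not say so. That rule is in the SAP ("The primary analysis will include all randomised participants with baseline and at least one post-baseline measure"), and handling of a missing baseline is properly left there.
- **That every baseline safety measure is compromised.** Section 4.7.1.2 already schedules the neonatal skin score at screening, and the eligibility criterion needs it. Temperature is an instrument reading analysed before against after each application (4.10.4), so it belongs immediately before application.
- **That late collection of history biases the co-primary effect.** The protocol's model adjusts for the baseline value of the outcome, not for history.

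**Conclusion.** The point holds as a design weakness that can be removed cheaply. It is not a demonstrated bias. For the co-primary swabs and the first maternal toxicity score, baseline follows randomisation in an open-label trial, and no earlier value exists to fall back on. Baseline could therefore differ or be missing by arm, and the all-randomised population in 4.10.4 can include people with no baseline.

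The size is unknown. The shift of 0.2 log10, the slope of 0.3 to 0.7 and the 5 to 20% loss are assumptions that show scale only; a same-day gap makes the upper end of the loss range look unlikely. Separately, the conflicting timings for baseline data and for the first neonatal skin score need one answer whatever view is taken of bias.

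**What to change.** - In 4.7.1, 4.7.2 and Tables 1 and 2, take the baseline swabs and the first maternal toxicity score after consent and immediately before the allocation is retrieved on the mobile device, in the same visit and examination.
- In 4.7.2, define baseline as that pre-allocation swab.
- Leave the pre-application temperature and the other pre-application safety checks where they are.
- Reconcile when baseline data are collected (4.6.2 and Table 2 against 4.7.1.1 and 4.7.1.2) and when the neonatal skin score is first taken (screening in 4.7.1.2 against the day-0 visit in Table 2).

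The cost is a protocol amendment and a reordered visit, with no added type of assessment. A few consented people may be swabbed and then not randomised. Allocation and container labelling (4.6.2.4) will fall between swab and application, so the step has to be rehearsed to avoid prolonging or repeating the examination. The change does not blind later swabs.

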**Table 3: Schedule of swabs from maternal and neonatal strata**

|                               | Maternal Strata*   |          |         | Newborns born to mothers from Maternal Strata# |          |         | Neonatal Strata*   |          |         |
|-------------------------------|---------------------------|----------|---------|------------------------------------------------------------------|----------|---------|---------------------------|----------|---------|
| Time from intervention | Frequency of intervention |          |         | Frequency of intervention                                        |          |         | Frequency of intervention |          |         |
|                               | Single                    | Multiple | Control | Single                                                           | Multiple | Control | Single                    | Multiple | Control |
| Post Delivery          |                           |          |         | ✓                                                                | ✓        | ✓       |                           |          |         |
| Baseline               | ✓                         | ✓        | ✓       |                                                                  |          |         | ✓                         | ✓        | ✓       |
| 4 hours                | ✓                         | ✓        | ✓       |                                                                  |          |         |                           |          |         |
| 8 hours                | ✓                         | ✓        | ✓       |                                                                  |          |         |                           |          |         |
| 12 hours               |                           |          |         |                                                                  |          |         |                           |          |         |
| 16 hours               |                           |          |         |                                                                  |          |         |                           |          |         |
| 20 hours               |                           |          |         |                                                                  |          |         |                           |          |         |
| 24 hours               | ✓                         | ✓        | ✓       |                                                                  |          |         | ✓                         | ✓        | ✓       |
| 28 hours               | ✓                         | ✓        | ✓       |                                                                  |          |         |                           |          |         |
| 32 hours               | ✓                         | ✓        | ✓       |                                                                  |          |         |                           |          |         |
| 48 hours               |                           |          |         |                                                                  |          |         | ✓                         | ✓        | ✓       |
| 72 hours               |                           |          |         |                                                                  |          |         | ✓                         | ✓        | ✓       |

\*Participants will be swabbed as per schedule or until delivery/birth (maternal strata) or discharge from the hospital (neonatal strata), whichever comes first.

#Newborns born to women from the maternal strata will be swabbed only once immediately after birth and will not receive any interventions.

Swabs will be vortexed in liquid transport medium, inoculated in serial dilutions on MacConkey and blood agar, and read after 24 hours incubation. Both total bacterial load (total CFU) and pathogen species will be recorded. Simultaneous inoculation onto extended spectrum beta-lactamase producing selective CHROMagar will be used to identify ESBL-E. Species identity will be confirmed by API.

Consent will be gained for use of samples in future microbiological analyses.

Swabs will be processed in the Malawi-Liverpool-Wellcome Trust microbiology laboratory, Blantyre. They will be securely couriered there from the trial site, using appropriate methods to control sample temperature. Two swabs will be taken and one disposed of after primary microbiological processing, and clones of bacteria will be kept in the Wellcome Trust research laboratory, Blantyre. The second

swab will be retained for up to 5 years to permit future microbiological analysis of the vaginal microbiota. Further details are outlined in the MOP.

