### **All maternal participants:**

Toxicity assessment: the toxicity assessment will include both questions about symptoms (of irritation) and a visual inspection of the vulval area (for erythema, skin breakdown and swelling) by trial staff. The assessment will take place immediately before the swabs at 4 hourly intervals during working hours on day 1 and day 2, or until birth if sooner and post delivery. More details can be found in [Section 4.7.3](#) and [Appendix II](#).

Swab: Swabs (low vaginal and perineal) will be taken at baseline (0 hr) and then 4 hourly on day 1 and day 2 (during working hours), or until birth (whichever is first). The swab timing will be recorded in a CRF. See MOP for further details on how to take swabs.

If the vaginal and perineal area is heavily soiled prior to the swabs and antiseptic application, it will be cleaned, as per routine clinical practice. Further details can be found in the MOP.

Swab of babies: Babies born to enrolled mothers will have swabs (peri-rectal/rectal and cervical/neck) collected after birth to assess bacterial load. The time this is taken will be recorded.

Final follow-up: On day 28 (+/- 7 days) after enrolment, final follow up will occur either by phone call or hospital visit. If a hospital visit is chosen, appropriate compensation will be provided for travel and time in line with local standard policies. Vital status will be ascertained, together with occurrence of adverse events (including clinically defined sepsis and any unscheduled visits to healthcare providers) and follow up of any reported potential side effects that were present.

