#### **4.7.7. Recruitment team**

Recruitment will be led by research midwives who will be employed by MLW. They will be responsible for approaching and recruiting participants, and for completion of trial procedures. Training in trial methodology will be led by the trial management group in collaboration with MLW. Training on GCP and clinical trials methodology will be led by MLW. This will include training before the trial commences, and regular refresher training and quality control exercises.

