| TOTAL funded by MRC                                                    | £ 112,472.41 | £ 109,995.40 | 111,207,117.85 MWK |

Converted using [https://ec.europa.eu/info/funding-tenders/how-eu-funding-works/information-contractors-and-beneficiaries/exchange-rate-infoeuro\\_en](https://ec.europa.eu/info/funding-tenders/how-eu-funding-works/information-contractors-and-beneficiaries/exchange-rate-infoeuro_en)

Rates as of December 2020 £1= 1011.01608MWK

| Cost                           | Justification                                                                                                                                                                                                                                                                           |
|--------------------------------|-----------------------------------------------------------------------------------------------------------------------------------------------------------------------------------------------------------------------------------------------------------------------------------------|
| Staff –directly incurred Posts | One and a half midwives in Malawi will be necessary to consent and recruit women and to administer the intervention to women and to infants. The study will recruit over 6 months. We will employ midwives for 9 months to allow for training and for any necessary follow up following |

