#### **4.5. Follow-up**

The following metrics will be presented by strata:

- Baseline swab: n(%) yes
- Number of swabs: median (IQR)
- Time in hours from baseline when each swab taken: median (IQR)
- Number of skin score assessments: median (IQR)
- Last time point of skin score assessment: : n(%) 0/4/8/24/28/32h in maternal strata and 0/1/2/3d in neonatal strata
- Day 28 follow-up: n(%)

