### **4.7. Secondary efficacy outcome analyses**

Note that no efficacy outcome data will be presented at the interim analysis.

Analysis of bacterial load in neonates exposed to maternal antiseptic will be as per primary outcome analyses described above.

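### The single newborn swab has no fixed time window, and the inherited primary model does not fit it: its time term is not defined as age at swab, and there is no newborn baseline

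*Protocol*

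**What the plan says.** **Timing.** The Table 3 footnote in protocol section 4.7.2 says that newborns of enrolled mothers "will be swabbed only once immediately after birth". Section 4.5 says at birth, and Table 1 says post delivery. Section 4.7.1.1 says these babies "will have swabs (peri-rectal/rectal and cervical/neck) collected after birth to assess bacterial load. The time this is taken will be recorded", and the text of section 4.7.2 adds: "The timing of these swabs will be recorded on a CRF". None of these places gives a window in minutes or hours.

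**Staff.** Of the research midwives, section 4.7.7 says: "They will be responsible for approaching and recruiting participants, and for completion of trial procedures". The budget justification in section 10 says: "One and a half midwives in Malawi will be necessary to consent and recruit women". Sections 4.6.2.2 and 4.7.1.1 place the mother's applications, swabs and toxicity assessments in working hours. No section describes who swabs a baby born outside them.

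**Analysis.** SAP section 4.7 says: "Analysis of bacterial load in neonates exposed to maternal antiseptic will be as per primary outcome analyses described above". The primary model in SAP section 4.6 takes change in total log CFU from baseline as its outcome. It has fixed effects for antiseptic, frequency, hour of swab (continuous) and baseline CFU, with individual as a random effect. SAP section 4.5 summarises swab times in hours from baseline.

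**The concern.** Protocol section 4.7.2 gives this swab the job of estimating what the maternal intervention does for the newborn, and section 1 lists maternal versus neonatal administration among the open questions. Skin load may rise in the hours after birth. If age at swab varies and the model does not account for it, that variation goes into the residual and widens the confidence intervals of an outcome with only 21 babies per arm.

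The inherited model was built for repeated swabs on one person with a pre-treatment value. A newborn has neither, so several of its terms have no clear meaning for this outcome.

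**Working it through.** **1. Does the timing wording agree?** The phrases run from immediately after birth (Table 3) through at birth (4.5) to after birth or post delivery (4.7.1.1, 4.7.2, Table 1). They can be read together, but only the strictest fixes a time, and it has no tolerance.

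**2. Can immediate swabbing be assumed?** The working week is not stated. Assume 37.5, 40 or 45 h per full-time post and no overlap of shifts. Cover is then 1.5 × hours / 168 = 33%, 36% or 40% of the week. Without other cover, some babies would wait.

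**3. Does the primary model fit one swab per baby?**

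- *Hour of swab.* No origin is defined for newborns. On the from-baseline scale of SAP 4.5, the origin would be the mother's baseline. The term is then her time to delivery plus the baby's age, and mainly the former.
- *Change from baseline and baseline CFU.* The baby has no baseline swab.
- *Individual random effect.* With one record per baby it cannot be separated from the residual.

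**4. The plan's own power figures.** None is given for the newborn outcome; the nearest are those per stratum. Detectable difference = (z for 1−α/2 + z for power) × √(1/n₁ + 1/n₂). For antiseptic versus control (42 vs 21, α = 0.012, 90% power): (2.512 + 1.282) × 0.267 = 1.014 SD, against 1.01 stated. At 80% power the formula gives 0.896 against 0.88 stated, and power at 0.88 is 0.78. The figures reproduce within tolerance.

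**5. What could an age term recover?** The documents give no delay distribution and no growth rate, so everything here is assumed.

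*Delay.* Births are even over 24 h, the staffed window is w = 8 to 12 h, and out-of-hours babies are swabbed when staff return.

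- Mean delay = (24−w)²/48: 5.3 h for w = 8 and 3.0 h for w = 12.
- Maximum delay = 24−w: 16 h and 12 h.

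*Load.* L(age) = L₀ + (8.4 − L₀)(1 − e^(−age/τ)). The 8.4 is the day-8 mean in the SAP appendix, used here as a plateau. L₀ is either 0 or 4.5, the appendix's neonatal prior mean reflecting recent birth. Residual SD is 3 (appendix) or 2 (assumed).

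*Gain.* With V the variance of L at swab and R² its squared correlation with age, the SE ratio is √(1 − R²·V/(V + SD²)).

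For τ = 15.6 h and SD 3:

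| L₀ | w | V | V/(V+SD²) | R² | SE cut |
|---|---|---|---|---|---|
| 0 | 8 h | 3.79 | 29.6% | 0.986 | 15.8% |
| 0 | 12 h | 2.45 | 21.4% | 0.993 | 11.3% |
| 4.5 | 8 h | 0.82 | 8.3% | 0.986 | 4.2% |
| 4.5 | 12 h | 0.53 | 5.5% | 0.993 | 2.8% |

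Over τ from 8 to 48 h, SD 2 to 3 and both starting loads, the cut runs from about 0.5% to 39%.

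**6. Cross-check with linear growth.** Assume growth g of 0.05 to 0.2 log₁₀ per hour, and delays uniform up to 16 h in 30% to 65% of births. SD inflation = √(1 + g² × Var(delay)/SD²).

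- At SD 3 the inflation is 0.3% to 6%. The 80%-power difference against control moves from 0.88 to at most 0.93 SD.
- At an outcome SD of 1, delays up to 16 h inflate it by 2% to 46%.
- With delays of 2 h or less it is under 1% at any SD from 1 to 3.

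**The case against.** The looser timing phrases do not contradict the strict one. The working-hours limits attach to the mother's procedures, not to the newborn swab. The midwife figure is a budget line written for six months' recruitment, whereas section 4.5 expects about twelve. A window and out-of-hours cover may be in the manual of operations. All of this stands, so delay is a possibility and not a documented fact.

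A reader might infer that the analysis ignores swab time altogether. It does not: a continuous hour-of-swab term is inherited, and the swab time is recorded. The defect is that the term's origin is undefined for newborns and that the only scale given starts at baseline.

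A reader might also infer that hours of bacterial growth distort the maternal effect. The documents do not support this. Delay driven by time of birth is unrelated to the randomised arm, and the laboratory is blinded. Open allocation makes unequal delay conceivable, but nothing shows it.

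Finally, a gain of 11% to 16% needs zero load at birth, yet load acquired from the mother at birth is what this swab is meant to detect.

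**Conclusion.** The point holds as a minor, free improvement. The timing wording is uneven and has no window; that part rests on the protocol alone. The model carried over by SAP section 4.7 does not fit a single swab without a baseline, and its time term is not age at swab.

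What is at stake is precision on one secondary outcome. The size cannot be derived from the documents. If load starts at 4.5, with τ 15.6 h and SD 3, the standard error falls by 3% to 4%. Across all the curve assumptions tried it falls by about 0.5% to 39%, and if swabs are truly immediate there is no gain. The documents do not establish bias between arms, or that many babies will be swabbed late.

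**What to change.** - **Protocol.** Use one wording for the newborn swab time in sections 4.5, 4.7.1.1 and 4.7.2 and in Tables 1 and 3, with a window, and say who takes the swab outside working hours.
- **SAP section 4.7.** Replace the cross-reference by a model of its own: ordinary linear regression of newborn total log CFU at the single swab on antiseptic and frequency. Code the control arm so that the comparison named in the outcome can be estimated. Put hours from birth to swab (continuous) in place of hour of swab. Drop change from baseline, the baseline CFU covariate and the individual random effect.
- **Reporting.** Show hours from birth to swab by arm, so that any difference in delay is visible.

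The cost is wording in both documents and about one degree of freedom. The swab time is already recorded; the interval also needs the time of birth.
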